# Summary

**Background:** **Background:** Maternal and newborn mortality and morbidity remain high in low- and middle-income countries such as Ethiopia. Limited access and dropouts from essential continuum of care interventions are critical factors. In Ethiopia about one in five complete the continuum of essential care through pregnancy, childbirth, and postnatal period Ethiopia. Evidence is limited on whether a package of interventions involving key community health actors increase the proportion completing essential maternal and newborn healthcare continuum in rural Sidama regional state, Ethiopia.

**Objective:** This study aims to implement and evaluate the effectiveness of community-based interventions designed to enhance involvement of key community health actors to improve completion rate of continuum of maternal care and utilization of newborn care.

**Methods:** Twenty rural kebeles (clusters) in Sidama Regional State, Ethiopia, are randomly allocated to intervention and control arms. A total of 2000 pregnant women, 1000 per arm, will be recruited between 20^th^ and 26^th^ week of gestation after intervention. Then they will be followed until six weeks postpartum between June 2024 and February 2025. In the intervention arm, mothers and newborns will receive targeted interventions at home and in their community through a package of interventions designed to improve completion rate of recommended maternal and newborn care. Control clusters will receive normal care from the state public health system. Primary outcomes will be the difference in the completion of continuum of maternal care and essential and emergency newborn care between intervention and control clusters measured by composite indicator constructed from variables. Secondary outcomes include rates of antenatal care completion, facility deliveries with skilled care, completion of at least four postnatal care, essential newborn care, and emergency identification and referrals, mortality measures.

**Conclusion:** This trial will implement and evaluate community-based intervention package within existing community healthcare infrastructure to produce evidence for informed policy and practice to achieve improved community-based healthcare.

**Budget:** A tentative budget plan will be **2,569,415**birrs, which will be secured from NORHED-II (SENUPH-II) project.

Key words: continuum of care, maternal, neonatal health care, community resource group.

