**Outcome and process indicators**

The primary maternal outcome measure is the completion rate of essential maternal care. We define a continuum of care completion as follows:

1. fully completed care when a mother has received four or more antenatal care, delivered in a health facility with a skilled attendant, and received at least four postnatal care (first 24 hours, 48-72 hours, 7-14 days, and six weeks after delivery) from HEWs or other health professionals within the first month after delivery. Because maternal completion of these essential care components will have an implication for newborn health and survival, and essential newborn care is given simultaneously during delivery and postnatal care, the completion of essential newborn care will be analyzed in relation to the maternal completion rate.
2. Emergency home-based care when the delivery occurred at home and mother and baby received immediate visit at home by HEWs or a higher health professional.
3. Sub-analysis on the primary outcome will compare intervention with control clusters separately on antenatal care completion rate, rate of facility delivery, proportion of assistance received immediately form HEWs or other professionals when a birth occurred at home, and proportion of mothers who stayed at maternal waiting shelters immediate days before delivery.
4. Proportion received financial, transport, and family care support from community resource persons (COLs) when a support is critically needed.
5. The proportion of newborn babies received the four essential newborn care services (immediate and thorough drying, skin-to-skin contact, immediate breastfeeding initiation, and delayed cord clamping)
6. Emergency newborn sickness identification and referral rates.
7. Secondary outcome measure will be on whether the intervention affected reduction of neonatal mortality and stillbirth rates.

For newborn babies, we will measure and compare with the control arm the proportion of babies immediately put to breastfeeding and exclusively feeding until at least a month after birth, the proportion of babies received essential thermal care (wrapping in close, skin-to-skin contact to mother immediately, delayed baby bathing), baby resuscitation at home and in clinics, and proportion of babies received emergency treatment and referrals when they had danger signs.

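### The protocol does not fix whether newborn care is a primary outcome, and its definition of completion runs on into items that do not define completion

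*Protocol*

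**What the plan says.** **Summary.** The primary outcomes are plural: "Primary outcomes will be the difference in the completion of continuum of maternal care and essential and emergency newborn care". They are to be "measured by composite indicator constructed from variables", with no list of those variables. The next sentence gives the secondary outcomes, which include antenatal care completion and skilled facility delivery, and then "completion of at least four postnatal care, essential newborn care, and emergency identification and referrals, mortality measures".

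**Outcome and process indicators.** "The primary maternal outcome measure is the completion rate of essential maternal care". A lead-in follows, "We define a continuum of care completion as follows", and then seven numbered items:

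- Item 1 is "fully completed care when a mother has received four or more antenatal care, delivered in a health facility with a skilled attendant", plus at least four postnatal contacts.
- Item 2 is "Emergency home-based care when the delivery occurred at home and mother and baby received immediate visit at home by HEWs" or a higher professional.
- Item 3 is a sub-analysis of the primary outcome.
- Item 4 is support received from community leaders.
- Items 5 and 6 are essential newborn care, and newborn sickness identification and referral. Neither is labelled primary or secondary.
- Item 7 reads: "Secondary outcome measure will be on whether the intervention affected reduction of neonatal mortality and stillbirth rates".

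**Objectives.** Objective 1A defines the maternal composite as at least four antenatal contacts, facility delivery with a skilled provider, and at least four postnatal contacts. Objective 2 is a separate newborn objective covering essential care and the identification and referral of sick babies.

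**Sampling strategy and sample size.** One binary endpoint is used, completion of pregnancy, birth and postpartum care, at 20% against 30%. Alpha is 0.05 two-sided, power 80%, ICC 0.01 and cluster size 150. The result is 723 per arm, raised to 1000 per arm, partly because several outcome measures may need more participants.

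**The concern.** A trial needs one statement of what counts as success. Here essential and emergency newborn care are primary in one sentence of the Summary, secondary in the next, and unlabelled in the section that should settle the matter. The wording of that section, which speaks of the primary maternal outcome, could even imply a newborn primary that is never named.

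With results in hand, the Summary would support a confirmatory newborn claim if the newborn result were favourable, and its demotion to secondary if it were not. The stated 5% error rate is secure only if the primary outcome is single and fixed in advance.

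The lead-in over the numbered list adds a second uncertainty. Taken literally it makes every item part of the definition of completion, including a home birth with an immediate visit, although item 1 requires facility delivery.

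**Working it through.** **1. The stated sample size, and the endpoint it covers.** Inputs, all from Sampling strategy and sample size: p1 = 0.20, p2 = 0.30, z = 1.96 and 0.84, m = 150, ICC = 0.01.

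- Individual-level n per arm = (1.96 + 0.84)² × (0.20×0.80 + 0.30×0.70) / 0.10² = 7.84 × 0.37 / 0.01 = 290.08.
- Design effect = 1 + (150 − 1) × 0.01 = 2.49.
- n per arm = 290.08 × 2.49 = 722.3, or 723.1 with exact z-values. This agrees with the stated 723. The last factor as printed, (1 + m − 1) × ICC, would give 290.08 × 1.5 = 435, so 723 comes from the usual design effect and the printed brackets are misplaced.

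The calculation contains no newborn rate, no split of alpha and no rule that several outcomes must all succeed. It fits one primary outcome, maternal completion.

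**2. The labels side by side.**

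| Outcome | Summary | Outcome and process indicators |
|---|---|---|
| Maternal completion | Primary | Primary (item 1) |
| Essential newborn care | Primary and secondary | No label (item 5) |
| Emergency newborn identification and referral | Primary and secondary | No label (item 6) |
| Antenatal completion, facility delivery | Secondary | Sub-analysis of the primary (item 3) |
| Mortality | Secondary | Secondary (item 7: neonatal death and stillbirth) |

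**3. How many primary outcomes this allows.**

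- One: maternal completion alone, or a single joint composite. If a joint composite required every component, its rate could not exceed the maternal rate, so the 20% and 30% would not automatically carry over to it.
- Two: maternal and newborn, matching the two numbered objectives.
- Three: maternal, essential newborn and emergency newborn.

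**4. Familywise error if any one success sufficed, each tested at 0.05, independence assumed.**

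- One: 5%.
- Two: 1 − 0.95² = 9.75%.
- Three: 1 − 0.95³ = 14.3%.

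The protocol does not say that one success suffices; this is the least favourable rule. Positive correlation lowers the last two figures, and it is likely because the protocol says that essential newborn care is given at the same time as delivery and postnatal care.

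**5. Whether the planned size could carry several primaries.** Assume that every outcome is 20% against 30% with ICC 0.01 and m = 150. Under a Bonferroni split, n per arm = (z for the split alpha + 0.8416)² × 37 × 2.49.

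- Two outcomes (alpha 0.025, z = 2.241): 876.
- Three outcomes (alpha 0.0167, z = 2.394): 965.

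The planned 1000 per arm exceeds both. For three outcomes the margin is 35 per arm (3.5%), and no dropout rate is stated. With the realised average of 1000/10 = 100 per cluster, the design effect is 1.99 and three outcomes need about 771, so the margin is then wider.

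**6. The completion list.** Item 1 and Objective 1A agree on the maternal composite and both require facility delivery. Items 3 to 7 are plainly not definitions of completion: a sub-analysis, support received, newborn care, referral and mortality. The lead-in is therefore placed over a list that it does not describe. Item 1 has a fault of its own: one of its four postnatal contacts falls at six weeks, yet it places the contacts within the first month.

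**The case against.** The best defence is that the intended primary can be recovered. Objective 1A, item 1 and the sample size all point to the maternal composite. Listing components of a composite as secondary is also normal practice, and the Summary does so for the maternal components. A multiplicity rule may properly sit in the statistical analysis plan. These points stand, and they limit the damage. They do not settle the status of newborn care, because the Summary calls it primary in so many words. Which outcome is primary is for the protocol to state, and here it gives conflicting answers.

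Power is not the main harm. As shown above, 1000 per arm would cover a three-way split under the stated assumptions.

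Two stronger readings are tempting and not supported. A reader might infer that the protocol counts attended home births as completion. The text does not say so: item 2 carries its own label, item 3 reports assistance at home births as a separate proportion from facility delivery, and most of the list is plainly not definitional. The placement is ambiguous, no more. A reader might also infer that success could be declared on any of items 1 to 6. Nothing calls items 2 to 6 primary; item 3 describes itself as a sub-analysis, and item 4 measures uptake of the intervention's support. An error rate built on six endpoints has no basis here.

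**Conclusion.** The concern holds as a contradiction about newborn care. The Summary makes it primary and secondary, the outcome section leaves it unlabelled, and the sample size ignores it. The number of primary outcomes is one, two or three depending on the reading, with a familywise error of 5%, 9.75% or 14.3%. The two higher figures assume independence and a rule that any one success suffices, so they are upper illustrations.

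The misplaced lead-in is a lesser fault: it makes item 2 ambiguous but does not turn home births into completion. The maternal composite itself is stated consistently, apart from item 1's unreconciled six-week contact. The correction should be made before outcome data are analysed, because afterwards any choice between the two sections would be open to question.

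**What to change.** 1. In the Summary and in Outcome and process indicators, name item 1, the maternal composite of Objective 1A on which the sample size rests, as the primary outcome, tested at two-sided 5%.
2. Give newborn care one status in both places. Either make it secondary, or test it second in a fixed sequence, only if the maternal test succeeds. The sequence keeps a confirmatory test for Objective 2 without splitting alpha. If it is chosen, define the newborn outcome to be tested; essential care and emergency referral would each need their own place in the order.
3. Restrict the completion lead-in to item 1. Label items 2 to 6 as secondary or process indicators, and state that item 2 does not count towards completion.
4. In the same edit, reconcile item 1's six-week postnatal contact with its limit of the first month, since the primary outcome cannot be scored unambiguously while both stand.
5. Check the registered outcomes against the corrected wording.

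The cost is an edit to two sections, with no new data and no change in recruitment. The only substantive loss is that newborn care takes a lower place in the testing order, and under the fixed sequence it can be claimed only after a positive maternal result.

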# Acknowledgement

First, we would like to express our gratitude to Hawassa University's College of Medicine and Health Sciences, School of Public Health, for establishing and supporting this maternal and neonatal health research core group on a project that allows us to work as a research team. Second, we would like to express our heartfelt gratitude to professor [name] for his mentorship through the process of developing this proposal and prior application for funding. We also want to express our gratitude to [name], coordinator of NORED II (SENUPH-II) project at Hawassa University for the trust and support to this core research team. We appreciate Norwegian Program for Capacity Development in Higher Education and Research for Development (NORHED) for financing for the project through NORHED-II (SENUPH-II) funding program.

# Acronyms and abbreviation

ANC Antenatal Care

BCG Bacille Calmette- Guérin

BEmONC Basic Emergency Maternal and Neonatal Obstetric Care

CHW Community Health Worker

DE Design Effect

ECD Early Childhood Development

EDHS Ethiopian Demographic and Health Survey

EPI Expanded program of Immunization

FMOH Federal Ministry of Health

HC Health Center

HDSS Health Demographic Survey Sites

HDT Health Development Team

HEP Health Extension Program

HEWs Health Extension Workers

HIV Human Immuno-deficiency Virus

ICC Intra Cluster Correlation

ICMNCI Integrated community based Management of Newborn and Childhood illness

IFHP Integrated Family Health Program

IRB Institutional Review Board

IUCD Intra Uterine Contraceptive Device

LBW Low Birth Weight

MEDHS Mini Ethiopian Demographic Health Survey

NMR Neonatal Mortality Rate

PMTCT Prevention of Mother to Child Transmission

PNC Postnatal Care

PHCU Primary Health Care Units

PSBI Possible Serious Bacterial Infection

SBA Skilled Birth Attendant

SDG Sustainable Development Goal

SENUPH South Ethiopia Network of Universities in Public Health

SPH School of Public Health

STI Sexually Transmitted Illness

SRS Sidama Regional State

TBAs Traditional Birth Attendants

UNICEF United Nations International Children`s Emergency Fund

WDG Women Development Group,

WHO World Health Organization

**Introduction**

Global maternal and child mortality was remarkably reduced between 2000 and 2015 through efforts under Millennium Development Goals (MDGs). However, recent estimates by UN inter-agency highlight that the progress stagnated between 2016 and 2020 (1). In 2020, there were over 300,000 maternal deaths, 2.4 neonatal deaths, and another 1.9 stillbirths (2, 3). Furthermore, neonatal mortality, the death of a newborn baby within the first month of life, shares nearly half (47%) of mortality of under-5 children shows slow progress.

Over 99 percent of maternal and newborn deaths and severe morbidities and disabilities from pregnancy and childbirth occur in low-income and middle-income countries. Unfortunately, sub-Saharan Africa has the highest neonatal mortality rate in the world with 27 per 1000 live births (4), also contributing close to half (42%) of global stillbirths, the death of babies after 28^th^ weeks of gestation and before birth, in 2019 (5). Poor investments (6) and limited access to quality maternal and newborn care in resource-limited settings are important factors because one-third of the neonatal deaths occur within the first day and three-forth in the first week after birth (3). Estimates from modeling 75 high-burdened countries highlighted improved coverage of essential maternal and newborn care interventions could avert over two-third of neonatal deaths, one-third of stillbirths, and over half of maternal deaths every year (7) because 85% of newborn deaths are because of fetal asphyxia, preterm birth, intra-partum complications and neonatal infections (7).

Since the WHO’s Alma Ata declaration in 1978 (8), community-based interventions, intended to bring essential healthcare services closer to these hard-to-reach areas have emerged as important alternatives to improve maternal and newborn healthcare. However, the strategies and its success are not uniform across communities and countries.

Ethiopia, like other low-income countries, struggles with limited access to the life-saving interventions for maternal and newborn health to the larger part of its population living in the rural areas, underscoring the need for innovative and sustainable strategies to close the gap in adverse pregnancy and childbirth outcomes.

One such innovative approach is the Ethiopian Health Extension Program (HEP), a flagship national program rolled out in 2003 by Ministry of Health of Ethiopia (9). In each village of about 5,000 population, two women known as Health Extension Workers (HEWs) trained for one year in general health are placed in a satellite health post to provide health promotion and disease prevention services to residents. These women are permanent employee of Ethiopian government with monthly salary.

The Health Extension Program (HEP) has been instrumental in expanding access to primary healthcare services, demonstrating the feasibility and impact of deploying health extension workers (HEWs) in rural settings. From 2012, another voluntary network of about 30 women per village known as women development team (WDT) were introduced to support the works of HEWs, creating a strong network closer to households. Consequently, a systematic review by Yibeltal Assefa and colleagues showed that the HEP has significantly improved essential preventive and health promotion indicators HEP (10). Yet, concerning the skills of the HEWs to provide essential maternal and newborn care, a study identified up to 88% of HEWs had poor knowledge of neonatal danger signs and expressed that they are not confident enough to attend deliveries (11). This underscores the importance of an approach that improves their confidence, skills, and integration with health facilities.

Furthermore, a 2022 article by Tiruneh GT and colleagues demonstrated that overall, only one-fifth (20%) of women who initiated the first antenatal care completed the continuum of recommended essential care that combines completion of antenatal care, skilled birth attendance, and critical postpartum care (12).

One of the challenges in maternal and newborn care continuum in poorly organized health systems is low proportion of women having postnatal contact with competent health professionals. In 2022, WHO published guidelines for postnatal care and recommends at least four such contacts in the key time periods during the first 24 hours, 48-72 hours, one-two weeks and six weeks after birth (13). Without successful completion of postnatal care during these key periods, it is difficult to succeed in improving the continuum of care.

The low rate of completion of essential continuum of care highlights the importance of a community-based maternal and newborn care system that supports the mother, the baby and family through key community health stakeholders such as skilled and motivated community health workers, trained and convinced community opinion leaders and women support groups. A systematic review synthesized evidence from community-based interventions to improve maternal and newborn health by Zohra S Lassi and colleagues in 2015 showed that interventions with strong community involvement showed significant positive results compared to other community-based intervention without community involvement (14). Previous community-based intervention trials in low-resource settings have demonstrated the important benefits of community-based interventions (15-17). However, many of these trials have been limited by a narrow focus of addressing specific factors, overlooking the complex and interconnected nature of the various community-based actors and stakeholders that influence healthcare utilization in rural communities.

Considering these challenges, this protocol outlines a comprehensive approach to conducting cluster randomized rural trials implementing a package of interventions that includes enhancing involvement of several community actors. The current intervention includes training and supervision and evaluate the effectiveness of these interventions in improving the completion of maternal continuum of care and newborn essential care.

Our hypothesis is that the proposed community-based intervention package intended to engage a broad spectrum of key actors, including community health workers, women's support groups, influential community leaders, local social welfare scheme systems (known as IDIR in Ethiopia), and the linkages between community and health facility services has a potential to improve maternal and newborn healthcare continuum care outcomes compared to control group receiving the routine public health services. Continuum of maternal and newborn care is a continuity of care during pregnancy, childbirth, and postpartum period with coordinated efforts from home through the health facility (18). To achieve improved rate of completion of the continuum of care, we aim to address the complex barriers such as poor knowledge of the importance of initiation and continuation of care until completion of standard care, transport barriers, and family care related challenges when a mother or baby needs to travel to reach care.

